**Fig. 1 Fig1:**
[figure not shown]
Study flowchart. LH, luteinizing hormone. LN2, liquid nitrogen. UMCU, University Medical Centre Utrecht. IUI, intrauterine insemination. IVF, in vitro fertilization. EGP, endometrial genetic profile. The boxes in pink apply to the nested cohort study

**Fig. 2 Fig2:**
[figure not shown]
Study time schedule according to SPIRIT (Standard Protocol Items: Recommendations for Interventional Trials)-t1, pre-study period. t0, allocation. t1, post-allocation period; women allocated to the endometrial scratch will undergo this procedure in the same or next month after randomization, in the luteal phase of the natural cycle (6 to 7 days after a positive ovulation test). t2, 12 months after allocation, at which a follow-up questionnaire will be sent to all women who have completed 12 months of follow-up. t3, period in which follow-up of women with an ongoing pregnancy, within 12 months after randomization, will continue until live birth. t4, close-out period. SAE, severe adverse events

### Follow-up

The follow-up duration is 12 months from the moment of randomization. Each centre registers whether a patient has conceived during the follow-up period. When a woman has become pregnant, she will undergo ultrasounds at 7–8 weeks and 10–12 weeks of gestation, after which she will continue her prenatal visits with her midwife or gynaecologist. The outcome of her pregnancy will be obtained after her due date by a structured questionnaire.

Data on all pregnancies and further fertility treatment(s) within 12 months after randomization will be obtained by a structured questionnaire. If available, this information will also be extracted from the electronic patient file.

### Monitoring

Monitoring will be performed by a monitor from the Dutch Consortium for Healthcare Evaluation in Obstetrics and Gynaecology. Furthermore, we have installed a Data and Safety Monitoring Board (DSMB) from the Dutch Consortium for Healthcare Evaluation and Research in Obstetrics and Gynecology. Roles of the DSMB include monitoring for evidence of treatment harm, such as serious adverse events, and advising on continuation or termination of the trial. Interim analyses have not been planned.

### Data collection and data analysis

Data will be collected in a web based registration system. Database cleaning will consist of internal consistency checks and identification of database entries outside expected ranges. Analysis will primarily be conducted according to the intention-to-treat principle. In case many women allocated to the intervention group ended up not having the scratch procedure (or vice versa), a per-protocol analysis may also be performed to clarify whether there may have been an underestimation of the magnitude of effect. The researchers performing the data collection and data analysis are not blinded to group allocation.

SPSS Statistics (IBM Corporation, Armonk, NY, United States), R (R Foundation, New Zealand) and Excel (Microsoft, Washington, United States) will be used to perform the statistical analysis. The primary and secondary outcome variables (except the costs, of which analysis is described below) will be compared between the treatment arms and expressed as relative risk with 95% confidence interval. A *p*-value less than 0.05 will be considered to indicate a statistically significant difference.

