### Sample size calculation

A total of 792 women will be included in the RCT of which we expect 150 to be included in the embedded study. Based on previous studies, the estimated difference in live birth rate is at least 10% between the patients with and without endometrial scratch (live birth rate respectively 45% vs. 35%).To detect such a difference with 80% power, 396 patients are needed per study arm, resulting in 792 patients in total. This number takes into account an estimated dropout rate of 5%.

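### The optional per-protocol analysis cannot reliably show whether intention-to-treat underestimates the effect of scratching, because exclusion can depend on whether a woman conceives

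*Protocol article*

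**What the plan says.** In the protocol article, Data collection and data analysis, the primary analysis is clear: "Analysis will primarily be conducted according to the intention-to-treat principle". A second analysis is optional and is considered only if many women in either arm did not follow their allocation. Its purpose is stated: "a per-protocol analysis may also be performed to clarify whether there may have been an underestimation of the magnitude of effect". The section adds: "The researchers performing the data collection and data analysis are not blinded to group allocation".

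Four other places decide who such an analysis would exclude.

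- **Timing of the scratch.** The Fig. 2 legend says that "women allocated to the endometrial scratch will undergo this procedure in the same or next month after randomization". Under Follow-up, the 12 months are counted from randomisation.
- **Start of timed intercourse.** Study procedure gives two accounts. It opens by placing the scratch ahead of the six months of timed intercourse, and it closes by starting those months at randomisation in both arms.
- **Avoiding pregnancy.** Study procedure tells women to avoid pregnancy in the cycle of the scratch. It mentions no other cycle.
- **Access for controls.** Recruitment, consent and randomization states that there is neither blinding nor a sham. The Discussion says that scratching is in frequent use in subfertility.

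**The concern.** A per-protocol comparison measures dilution only if the women removed from one arm have the same prognosis as women who stay in the other. Here two routes break that balance.

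1. A scratch-arm woman who conceives between randomisation and her scratch appointment would not be scratched. Per-protocol removes her, usually as a success. Her counterpart in the control arm has followed her allocation and is kept.
2. A control can seek a scratch only while she is not pregnant. Removing crossovers therefore tends to remove women who have so far failed to conceive, which raises the control rate.

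Both routes lower the apparent effect, which is the error the analysis is meant to detect. A third route runs the other way: if women who skip the scratch have a poor prognosis, removing them flatters the scratch arm. A reader who sees the per-protocol figure move cannot tell dilution from selection.

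**Working it through.** **Inputs from the plan.** Sample size calculation: "live birth rate respectively 45% vs. 35" per cent; "To detect such a difference with 80% power, 396 patients are needed per study arm"; "This number takes into account an estimated dropout rate of 5" per cent. Data collection and data analysis: p "less than 0.05 will be considered to indicate a statistically significant difference" (two-sided assumed). The plan gives no rate of, or reasons for, non-receipt, so every such share below is an assumption.

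**Plan's own figure.** n = [1.96·√(2·0.40·0.60) + 0.8416·√(0.45·0.55 + 0.35·0.65)]² / 0.10² = 376 per arm, and 376/0.95 = 396. It reproduces.

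**Route 1, conception before the scratch.** A 35% live birth rate over 12 months at a constant hazard gives 1 − 0.65^(1/12) = 3.5% per month. Let x be the share of the scratch arm conceiving to live birth before the scratch.

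- Per-protocol scratch rate = (0.45 − x)/(1 − x). The control rate stays at 35%.
- The like-for-like control rate, without the matching early conceivers, is (0.35 − x)/(1 − x). The effect of receipt is therefore 0.10/(1 − x).

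| x | Per-protocol scratch rate | Per-protocol difference | ITT difference | Effect of receipt |
|---|---|---|---|---|
| 0 | 45.0% | 10.0 | 10.0 | 10.0 |
| 2% | 43.9% | 8.9 | 10.0 | 10.2 |
| 3.5% | 43.0% | 8.0 | 10.0 | 10.4 |
| 7% | 40.9% | 5.9 | 10.0 | 10.8 |

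At x = 3.5% the relative risk falls from 45/35 = 1.29 to 43.0/35 = 1.23, while among women who receive the scratch it is 43.0/32.6 = 1.32. With no true effect (35% in both arms), x = 2% and 3.5% give per-protocol differences of −1.3 and −2.4 points. The 7% row needs about two months of unprotected exposure before the scratch. Given the Fig. 2 timing and the instruction to avoid pregnancy, 0 to 3.5% is the more realistic range.

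**Route 2, controls scratched later.** At the same hazard, √0.65 = 80.6% of controls have not conceived to live birth by month 6. Suppose 5%, 10% or 20% of them are then scratched (4.0%, 8.1% or 16.1% of the arm). Without a scratch, their chance over the next six months is 19.4%; at the scratch-arm hazard it is 1 − √0.55 = 25.8%. With s the share crossing over:

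- ITT control rate = 0.35 + s·(0.258 − 0.194) = 35.3%, 35.5%, 36.0%.
- Per-protocol control rate = (0.35 − 0.194·s)/(1 − s) = 35.7%, 36.4%, 38.0%.

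Against 45%, the ITT differences are 9.7, 9.5 and 9.0 points and the per-protocol differences 9.3, 8.6 and 7.0. Per-protocol lies further from 10 each time. ITT/(1 − s) gives 10.1, 10.3 and 10.7: nearer, but slightly high, because a late scratch is counted as equal to an early one.

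**Route 3, scratch skipped for other reasons.** Let 10% of the scratch arm go unscratched with live birth rate q. The remaining 90% have control rate r = (0.35 − 0.10·q)/0.90 and scratched rate r·(45/35).

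| q | ITT difference | Per-protocol difference | Effect of receipt | ITT/0.90 |
|---|---|---|---|---|
| 10% | 9.7 | 13.6 | 10.8 | 10.8 |
| 20% | 9.4 | 12.1 | 10.5 | 10.5 |
| 35% | 9.0 | 10.0 | 10.0 | 10.0 |
| 50% | 8.6 | 7.9 | 9.5 | 9.5 |

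Per-protocol overshoots when non-receivers have a poor prognosis, is right when their prognosis is average, and falls below ITT when it is good. Dividing the ITT difference by the difference in receipt recovers the effect in every row.

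**The case against.** The strongest reply is that little rests on this analysis. It is optional and explanatory, and the threshold for many and the per-protocol definition are details an article commonly leaves to the full protocol or analysis plan. That stands, and the missing threshold is not counted here. What remains is the article's own choice of per-protocol as the tool for detecting dilution.

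The trigger also weakens route 1. If few women miss the scratch, the analysis is not run. If many do, early conception cannot explain most of it, and refusal or scheduling must dominate. Where those reasons are unrelated to prognosis, per-protocol gives 10.0 points and ITT 9.0, so it does its job. This stands too, but nothing in the plan would show that this case applies.

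That controls would seek a scratch after failing to conceive is an inference from the open design. The Discussion speaks of subfertility in general, not of couples under expectant management.

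A reader might infer something stronger. Stacking 5% of the scratch arm conceiving early (85% live birth) on 10% of controls crossing over (10% live birth) gives (0.45 − 0.0425)/0.95 − (0.35 − 0.01)/0.90 = 42.9% − 37.8% = 5.1 points. That joins two assumed extremes, and the documents support neither. Nor do they say that the unblinded researchers would decide on the analysis after seeing results; they say only that collection and analysis are unblinded.

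**Conclusion.** The point holds at modest size. Per-protocol cannot be relied on to show whether ITT underestimates the effect, because exclusion can depend on outcome and the direction of bias is not known in advance. With an assumed 0 to 3.5% of the scratch arm conceiving to live birth before the scratch, a 10-point difference becomes about 10 to 8 points, while the effect of receipt is 10.0 to 10.4. This rests on the plan's 45% and 35%, a constant monthly hazard, and at most about one unprotected month before the scratch.

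It would be wrong to conclude that the trial's main result is at risk, that per-protocol is always biased, or that its bias always runs against scratching. ITT is primary and unaffected, non-receipt unrelated to prognosis leaves per-protocol unbiased, and poor-prognosis non-receipt biases it upward. Nothing here requires per-protocol to be banned.

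**What to change.** For the dilution question, prespecify, for example:

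> The effect of receiving the scratch will be estimated in all randomised women as the complier-average causal effect, with randomisation as the instrument: the ITT risk difference divided by the between-arm difference in the proportion scratched, with a 95% confidence interval. The matching relative risk in compliers may be added. Reasons for non-receipt will be reported by arm. Any per-protocol analysis is exploratory and will not be taken as evidence of dilution.

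Separately, reconcile the two statements in Study procedure on when timed intercourse starts relative to the scratch, since they determine how much conception can occur before it.

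The cost is a few sentences and one short analysis, with three downsides to state.

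- **Wider interval.** With 376 analysed per arm, the ITT half-width is 1.96·√(0.475/376) = 7.0 points. At 10% non-receipt it becomes about 7.0/0.90 = 7.7, treating the divisor as fixed.
- **Allocation must act only through the scratch.** The pregnancy-avoidance cycle strains this, mainly for women who avoid conception but are never scratched. For the others the cycle is largely part of receiving the scratch.
- **Late scratches in controls count as equal to early ones.** The Background says the duration of effect is unclear. In route 2 this made the estimate 0.1 to 0.7 points too high.

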### Cost-effectiveness analysis

A cost-effectiveness analysis covering a period of 12 months will be performed parallel to the clinical trial for economic evaluation, which is designed from both a healthcare and societal perspective. This cost-effectiveness analysis will be based on live birth rate and average costs per patient, taking into account any additional fertility treatments patients undergo during these 12 months. The impact on patient’s life will be expressed in quality-adjusted life years (QALY). A decision model will be used to evaluate the optimal strategy, taking into account the time to pregnancy, (in) direct costs and estimated QALY. Additionally, the incremental cost-effectiveness ratio (ICER) and long-term costs, such as delivery and perinatal costs, will be determined. Sensitivity analysis will define robustness of the results.

## Discussion

Since a study in 2003 [18] reported improved implantation rates after endometrial scratching, this procedure has been getting increasing global attention. Even though conclusive scientific evidence on its beneficial effects is still lacking, endometrial scratching is frequently being performed in women with subfertility [16]. While this intervention might be favourable for patients undergoing IVF, the effectiveness remains unclear for women with unexplained infertility trying to conceive naturally or through IUI. Studies to date show a possible beneficial effect of endometrial scratching in the latter group of women [14]. However, the quality of this evidence is very low and therefore these results should be interpreted with caution. To give clarity on this topic, robust studies are needed.

If these studies can confirm a favourable effect of endometrial scratching in increasing the live birth rate, this intervention could be offered as a simple and cost-effective treatment for unexplained infertility. Consequently, this potentially avoids some patients undergoing more expensive and invasive treatments such as IVF [19]. On the contrary, if further studies show that there is no beneficial effect of endometrial scratching on live birth rate in women with unexplained infertility, this group should not undergo an intervention with additional costs and potential risks as pain and infection.

The current study will evaluate the effect of endometrial scratching on live birth in women with unexplained infertility who are trying to conceive spontaneously. In addition, this study seeks to identify whether endometrial genetic profiles (EGPs) can predict the chance of reproductive failure within one year in couples with unexplained subfertility, as Koot et al. (2016) have shown that an endometrial 303-gene expression profile can predict repeated implantation failure (RIF) in women undergoing IVF/ICSI (PPV 100%) [20]. Defective endometrial receptivity may contribute to the aetiology of unexplained infertility. Therefore identifying an EGP, that is related to impaired endometrial receptivity, could help clinicians in counselling and guiding treatment of women with unexplained infertility. Due to rapid developments in the field of genetics, we have not determined the exact design for analysis of these EGPs yet. As the strategy might implement some new techniques or new genetic markers, it will be finalized later. Until then, tissue will be stored for future research. Lastly, development of endometrial organoids will be part of the embedded study. In the past decade there has been a rediscovery of organoids, which are three-dimensional (3D), self-organizing and genetically stable cell cultures with cell types that resemble the tissue of origin [21–23]. One of their most valuable features is that organoids recapitulate key structural and functional properties of the specific organ they have been derived from [22]. Consequently, patient-derived organoids offer possibilities to mimic pathologies in a dish and develop personalized treatments [22]. Organoids can be generated from either 1) pluripotent stem cells, like embryonic stem cells (ESC) and induced pluripotent stem cells (iPSC) or 2) organ-restricted adult stem cells (aSC) [21]. For the development of endometrial organoids, aSC are used [17, 23]. As the human endometrium is highly regenerative, these aSC can be identified in adult endometrial tissue during the process of tissue damage repair and self-renewal [21, 24]. When conditions that mimic the stem cell niche environment are created around the aSC, these stem cells are induced to form organoids [21, 25]. In the current embedded study, endometrial tissue of women with unexplained infertility will be developed into endometrial organoids after broad informed consent. In Reproductive Medicine these would be the first endometrial organoids generated from cryopreserved biopsy catheter derived endometrial tissue. Previous endometrial organoids were created from fresh, non-frozen biopsy catheter derived tissue or laparoscopically obtained biopsies [17, 23]. The development of endometrial organoids will open possibilities for further research into endometrial receptivity and other endometrial disorders.

## Abbreviations

ART: Assisted reproductive technology
CAT: Chlamydia antibody titre
CPR: Clinical pregnancy rate
EGP: Endometrial genetic profile
ICER: International cost-effectiveness ratio
ICSI: Intracytoplasmic sperm injection
IUI: Intrauterine insemination
IVF: In vitro fertilization
LBR: Live birth rate
LH: Luteinizing hormone
OFO: Standard fertility work-up (in Dutch: oriënterend fertiliteits onderzoek)
QALY: Quality-adjusted life years
RCT: Randomized controlled trial
RIF: Repeated implantation failure
RNA: Ribonucleic acid
